### Objective

To determine the feasibility and acceptability of an online integrated parenting intervention for bipolar disorder compared with treatment as usual.

Main research questions:To demonstrate feasibility of recruitment and consenting procedures, adherence to intervention and retention to both arms of the trial across assessment, intervention and 16, 24, 36 and 48 week follow up periods.To provide parameter estimates of clinical outcomes with respect to, child behaviour, parenting skills, mood, and family functioning.

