### Sample size

The chief purpose of this trial is to evaluate the feasibility and acceptability of providing IBPI, thus a formal power calculation for a test comparing treatment groups is not appropriate.

The primary outcome, to demonstrate feasibility, will be recruitment into the trial and the proportion of completers of the intervention and of assessments at 16, 24, 36 and 48 weeks follow-up. Thirty participants per group, i.e. 60 in total, is sufficient to reliably determine the primary feasibility outcomes for the trial. We therefore aim to recruit N = 100 across both arms of the study to allow for a potential drop-out rate of up to 35-40 % based on an average of attrition rates across 4 relevant studies of web-based interventions for affective and/or parenting issues [20,24-26].

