#### Clinical and functional outcomes

Clinical and functional outcomes consist of repeated measurements. These will be taken at weeks 0, 16, 24, 36 and 48 following randomisation for most measures, except SCID-LIFE, HAM-D and MAS which will be recorded a 0, 24,and 48 weeks (but assessment of episodes covers all the weeks from the previous assessment). Records on participants who drop out of the study before week 48 will be incomplete. Analysis of measurements and dropout times will include checks that groups are balanced with respect to age, gender, level of education and use of services, and control for these as required, followed by linear modelling with correlated errors for the repeated measurements and linked logistic regression models for the probability of dropout conditional on the repeated measurements prior to dropout [41]. In order to inform the design of a definitive trial, these analyses will investigate which patient characteristics affect the repeated measurement outcomes and/or the probability of dropout.

To determine how well IBPI worked for those who did not drop-out, the main clinical outcome measure is D, the difference in SDQ and PS pre- and post-intervention. The corresponding primary analysis will be a two-sample t-test comparing values of D in the two groups. Post-intervention, it is hypothesised that participants who received IBPI will have a greater D than those receiving assessments only. We will also explore website usage data.

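### The main clinical comparison is an unadjusted t-test on raw change in SDQ and PS; adjusting for the baseline score already collected would usually be more precise

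*Protocol article*

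**What the plan says.** The subsection on clinical and functional outcomes in the Analysis section describes two analyses.

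The first is a longitudinal model: "linear modelling with correlated errors for the repeated measurements", linked to logistic models for dropout. It is accompanied by "checks that groups are balanced with respect to age, gender, level of education and use of services, and control for these as required". The baseline value of the outcome is not among the listed covariates.

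The second has its own purpose: "To determine how well IBPI worked for those who did not drop-out". For it, "the main clinical outcome measure is D, the difference in SDQ and PS pre- and post-intervention", and the method is fixed: "The corresponding primary analysis will be a two-sample t-test comparing values of D in the two groups". No adjustment is mentioned.

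Baseline scores are available. On the measurement times the same subsection says: "These will be taken at weeks 0, 16, 24, 36 and 48 following randomisation for most measures". Table 1 lists SDQ and the Parenting Scale at baseline and at 16 weeks, which it labels the end of the intervention.

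**The concern.** Subtracting the baseline score fixes its coefficient at 1. A linear model estimates that coefficient from the data. When pre and post SDs are equal, the best coefficient is r, which is below 1, so subtraction over-corrects. Two consequences follow, and they are one loss seen from two sides: the interval is wider than it need be, and an arm that starts worse by chance tends to show more change through regression to the mean.

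What is at stake is the precision of the SDQ and PS comparisons. One of the two main research questions is "To provide parameter estimates of clinical outcomes with respect to" child behaviour, parenting skills and other domains. With about 30 completers per arm expected, precision is limited.

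**Working it through.** **Inputs from the article.** Sample size section: 30 per group (60 in total) as the number needed, 100 recruited, dropout of up to 35-40%. Analysis section: about 60% expected to complete. These agree: 60/(1 − 0.40) = 100.

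**The article's own precision figure.** It gives one only for the completion proportion. 1.96 × √(0.6 × 0.4/100) = 0.096 and 1.96 × √(0.6 × 0.4/50) = 0.136, so the stated 9.6% and 13.6% reproduce. No precision is stated for D.

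**Assumptions.** Equal SD at baseline and follow-up (set to 1), pre-post correlation r from 0.3 to 0.9, n = 30 completers per arm (N = 60). The article gives neither the SDs nor r.

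**Formulas for the variance of the between-arm difference.**
- Change score: 2(1 − r) × 2/n.
- Baseline-adjusted: (1 − r²) × 2/n × [1 + 1/(N − 4)]. The bracket is the cost of estimating the slope: 1 + 1/56 = 1.018.
- Ratio, adjusted to change score: (1 + r)/2 × 1.018.

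**Example, r = 0.5.**
- Change-score SE = √(1.00 × 2/30) = 0.258. Half-width with t on 58 df (2.002) = 0.52.
- Adjusted SE = √(0.75 × 2/30 × 1.018) = 0.226. Half-width with t on 57 df (2.002) = 0.45.
- Ratio = 0.75 × 1.018 = 0.76. The gain is worth 30/0.763 = 39 per arm in place of 30.

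| r | Variance ratio | Half-width, change score (SD) | Half-width, adjusted (SD) | Equivalent n per arm |
|---|---|---|---|---|
| 0.3 | 0.66 | 0.61 | 0.50 | 45 |
| 0.5 | 0.76 | 0.52 | 0.45 | 39 |
| 0.7 | 0.86 | 0.40 | 0.37 | 35 |
| 0.8 | 0.92 | 0.33 | 0.31 | 33 |
| 0.9 | 0.97 | 0.231 | 0.227 | 31 |

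Simulation with 40,000 trials per value gave variance ratios of 0.665, 0.768, 0.864 and 0.968 at r = 0.3, 0.5, 0.7 and 0.9, in line with the formula.

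**Limits of the gain.** Setting (1 + r)/2 × 1.018 = 1 gives break-even at r of about 0.96. At the other end, 2(1 − r) exceeds 1 when r < 0.5, so there the change score is less precise than comparing follow-up scores with no use of baseline.

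**Baseline imbalance.** Given a baseline difference δ between arms, the change-score contrast shifts by (1 − r)δ in size. One standard error of chance imbalance is √(2/30) = 0.26 SD, which at r = 0.5 moves the estimate by 0.5 × 0.26 = 0.13 SD. This is not extra to the variance loss. Leaving out the slope cost, 2(1 − r) = (1 − r²) + (1 − r)², and the last term is the imbalance component.

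**The case against.** The strongest reply is that nothing here is an error. Under randomisation the t-test on change is unbiased and its interval has correct coverage. That stands: the point is lost efficiency. A reader might take the imbalance argument to mean that the planned estimate is biased. It does not, because chance imbalance averages to zero over randomisations and is already counted in the variance. Nor is adjustment better in every case: at 60 completers it stops paying near r = 0.96 and gains only about 3% of variance at r = 0.9.

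A second reply is that the longitudinal model includes week 0 among its repeated measurements and may already use the baseline score. It may, but the text does not say how. That model is separate from the t-test and is not the analysis called primary for D.

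Two stronger readings are tempting and not supported.
- A reader might infer that this t-test supplies the definitive trial's planning figures. The article attaches that role to the longitudinal and dropout models and gives the t-test a narrower purpose.
- A reader might infer that a primary significance test contradicts the statement that "a formal power calculation for a test comparing treatment groups is not appropriate". That statement declines a power calculation; it does not rule out a comparison. Primary here means primary for D, since the trial's primary outcome is feasibility and acceptability. No significance level or progression rule is tied to the test, and a t-test comparison also yields a mean difference and interval.

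**Conclusion.** The point holds as an avoidable loss of precision in the analysis that the article itself names as primary for D. Adjustment cuts the variance of the treatment difference by about 34% at r = 0.3, 24% at 0.5, 14% at 0.7, 8% at 0.8 and 3% at 0.9. The direction is secure for any r below about 0.96 under equal pre and post SDs. The size rests on that assumption, on an r that the article does not state, and on 30 completers per arm. Importance is moderate to low: these are clinical outcomes in a pilot whose primary outcome is feasibility, but estimating them is a stated research question and the improvement needs no new data.

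**What to change.** Replace the t-test on D with a linear model of the week-16 score on allocated arm and the baseline value of the same score, fitted separately for SDQ and PS. Report the adjusted difference between arms with its 95% CI.

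The change is to wording only, since the scores are already collected. The statistical cost is one degree of freedom, about 1.8% of variance at 60 completers. The change leaves the comparison restricted to those who did not drop out, with attrition of up to 35-40% allowed for. That needs separate attention.

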## Discussion

This study will provide important data for the development of a future definitive IBPI trial should the results of this trial look promising. The online parenting intervention IBPI has been developed with experts in positive parenting interventions, experts in the self-management of bipolar disorder and individuals who have experience of bipolar disorder consistent with Mental Health Research Network good practice guidelines [42]. In addition, service user involvement has been a core aspect of the research process, from inception of ideas through to the development of the methodology, outcome measures and the intervention. The intervention itself promotes positive parenting and builds upon skills which parents already possess. There is currently no other known intervention which specifically provides targeted support for parents with bipolar disorder.

Strengths of the study include a focus on an intervention which integrates strategies to aid living well with bipolar disorder in the context of being a parent of young children. It also offers the potential to increase access to evidence-based support for a group who currently have limited access to psychological interventions in general and particularly to interventions which also incorporate consideration of the challenges of parenting. The diverse nature of the research and intervention development team have ensured that the intervention is grounded in lived experience of being a parent with bipolar disorder, with the addition of opinions from experts in the field. The nature of IBPI means that each parent can personalise and tailor their own intervention, allowing them to get the most out of it for their circumstances. The intervention is intended to be both flexible and appealing, acknowledging the issue of engagement. All modules can be started, paused and recommenced when convenient or when feeling able to focus on the content.

The online RCT aims to be as rigorous as a traditional RCT but reducing the impact of potentially confounding variables such as extensive contact with the research team. In line with the definition of Mathieu *et al*. [43] the current trial is *primarily* rather than *fully* on line (as not all of the assessments are completed online). Participation in the trial is from home and observer-rated assessments are made via the telephone consistent with this minimal contact (whilst all self-report measures are completed online). A diagnosis of bipolar disorder is verified at baseline; followed by a series of outcome measures at baseline and then at follow up time points. Evaluating IBPI online makes it possible to recruit participants nationally, and capture outcome data instantaneously. This study is recruiting from across NHS primary and secondary care settings throughout the United Kingdom and through self-referral with a focus on online recruitment. Therefore, the findings should be more representative of a group of parents with bipolar disorder who use the internet for parenting support. This means higher levels of reliability, and validity without the cost implications and resources necessary in traditional RCTs.

The weaknesses of this study would need to be addressed in a later definitive trial. However, parenting in bipolar disorder is an area where little is known about the effects of a targeted intervention. The study allows individuals to be followed up for a period of 48 weeks following the use of the IBPI intervention. Further follow-ups would be helpful to indicate more definitively whether this intervention has a sustained impact on longer term parenting and mood outcomes. As the current focus of this trial is on parents of children from 3 to 10 it will not indicate whether this integrated approach might have potential as children enter teenage years and beyond (when risk for increased psychopathology in offspring is detected [44]).

The online nature of this intervention study means that there is a lack of human contact including the absence of a therapist. This potentially puts more demands on the individual to apply self-management strategies on their own initiative. However, this might also be an advantage for some participants, particularly in the context of evidence that individuals with bipolar disorder typically place high value on autonomy [45]. It has been suggested that computer mediated studies may provide an environment which encourages socially desirable or unreliable responding [46]. However, there is contrasting evidence to suggest that such studies are equally as reliable as traditional methods of outcome data collection [47] and it has been argued that the anonymous online environment allows participants to express their opinions and feelings more freely, thus, reducing unreliable responding when completing outcome measures online [48].

In summary, if the current study indicates that IBPI is an acceptable and feasible intervention, in addition to potential clinical benefits it will be an important step towards developing evidence-based interventions for parents with bipolar disorder that have been lacking until now.
